#### Sample size calculation: DISTINCT-2 study

In the intermediate VTE risk group, the cumulative incidence of symptomatic VTE within 90 days is expected to be 1.3%. With n=2500, the width of the 95% CI is expected to be 0.9% to 1.7%, with a probability of less than 15% that the upper bound of a two-sided 95% CI will exceed the 2% margin. We consider this a sufficiently precise estimate of VTE risk in this patient group.

#### Sample size calculation: DISTINCT-3 trial

By only including patients with a predicted VTE risk of >1.5%, a 90-day cumulative incidence of symptomatic VTE of 2.5% is expected in the control arm. This risk is based on the results from the development and validation studies of the TRiP(plasty) score.^18^ We expect that the intervention gives a relative risk reduction of 50% (ie, expected outcome in the intervention arm: 1.25%). This risk reduction was estimated from earlier dose-finding trials and our recently performed pilot study.^30^,^32^

At a two-sided alpha level of 0.05 and a power of 80%, 3694 patients would be necessary. To account for the interim analysis and thus testing against a slightly stricter statistical significance level at the final analysis, a total of 3748 patients are required (1874 per treatment arm). To account for a maximum dropout rate of approximately 9%, we aim to include 2050 patients in each arm, totalling 4100 patients.

For the DISTINCT-3 trial, we assume an increased relative major bleeding risk of 65% (from 0.5% to 0.83%) by increasing the thromboprophylaxis dose and duration. This estimate is based on results from earlier trials and our pilot study.^30^,^32^

### Statistical analysis

Both modified intention-to-treat (ITT) and per-protocol (PP) analyses will be performed.

#### Intercurrent events

Randomised patients who did not undergo surgery will be excluded from the ITT analysis. Treatment discontinuation will be ignored in the primary analysis. In a secondary PP analysis, we will only include patients who completely adhered to the study protocol. This means that they are not allowed to skip study medication. If this happens, patients will be excluded from the secondary analysis. We will report the proportion of patients who did not adhere to the study protocol, including details on the number of skipped dosages and the reasons for non-adherence.

Death as an intercurrent event will be included as an outcome event in the analyses (both in ITT and PP) if the outcome adjudication committee adjudicates this death as an outcome event (death related to a fatal PE or bleed). If death is not related to VTE or bleeding, it will be ignored in the analyses (as such an event is very rare within 90 days following surgery).

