### Study interventions

For the DISTINCT-1 trial, patients will be randomised between:

InterventionIn-hospital thromboprophylaxis only: any type of LMWH or DOAC in a prophylactic dose, as approved by the Dutch antithrombotic guidelines, administered until hospital discharge.^21^ The first dose of LMWH should be administered within 6–24 hours following surgery; the first dose of apixaban within 12–24 hours; the first dose of rivaroxaban within 6–10 hours and the first dose of dabigatran within 1–4 hours. The type of anticoagulant administered according to the local protocol (the same as that used in the control group). Patients undergoing outpatient THA or TKA (surgery and discharge on the same day) will receive one dose of thromboprophylaxis.ControlStandard thromboprophylaxis for 4 weeks: any type of LMWH or DOAC in a prophylactic dose, as approved by the Dutch guidelines.^21^ The first dose of LMWH should be administered within 6–24 hours following surgery; the first dose of apixaban within 12–24 hours; the first dose of rivaroxaban within 6–10 hours and the first dose of dabigatran within 1–4 hours. The type of anticoagulant administered is according to the local protocol.

DISTINCT-2 study

Standard thromboprophylaxis for 4 weeks: any type of LMWH or DOAC in a prophylactic dose, as approved by the Dutch guidelines.^21^ The first dose of LMWH should be administered within 6–24 hours following surgery; the first dose of apixaban within 12–24 hours; the first dose of rivaroxaban within 6–10 hours and the first dose of dabigatran within 1–4 hours. The type of anticoagulant administered is according to the local protocol.

For the DISTINCT-3 trial, patients will be randomised between:

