### Study follow-up

Primary and secondary outcomes will be assessed using a questionnaire at 2 weeks, 6 weeks and 90 days postoperatively. Additionally, patients who experience a symptomatic VTE, major bleed or PJI receive an additional questionnaire at 1 year postoperatively. Controls, 1:1 matched on age, sex, study centre and type of surgery, will receive the same questionnaire. All postoperative care is according to the current standard of care; no routine VTE screening will be performed. In the case of a (possible) outcome event, additional data on the event, including imaging studies, consult letters, discharge letters and any other relevant information, are collected from the medical record of the participant. In table 1, study procedures and assessments are presented.

**Table 1 T1:** An overview of study procedures and assessments

Evaluation	Preoperative	Day 0 (surgery)	2 weeks	6 weeks	90 days	12 months
Baseline characteristics, including age, sex, BMI, comorbidities and VTE risk factors	X					
Perioperative outcomes*		X				
Outcome event(s) by questionnaire			X	X	X	
Treatment compliance (questionnaire)				X		
VAS	X				X	
OHS/OKS	X					
EQ-5D	X				X	
In case of an outcome event(s) and controls						
OHS/OKS						X
SF-36						X
EQ-5D						X

* Perioperative variables are derived from the Dutch Arthroplasty Registry (LROI).

BMI, body mass index; EQ-5D, EuroQol 5-Dimensions Quality of Life Questionnaire; LROI, Landelijke Registratie Orthopedische Interventies; OHS, Oxford Hip Score; OKS, Oxford Knee Score; SF-36, 36-Item Short Form Survey; VAS, Visual Analogue Scale; VTE, venous thromboembolism.

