### Analysis of primary endpoints

#### DISTINCT-1 statistics

A primary modified ITT analysis and a secondary PP analysis will be performed. The overall cumulative incidences of symptomatic VTE and major bleeding between the control and intervention groups will be compared, using a one-sided non-inferiority analysis for the absolute risk difference, with a significance level set as a one-sided p value of 0.025.

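### The per-protocol set tolerates no missed dose and has no cut-off at the first outcome event, so it selects patients unequally between arms whose dosing periods differ greatly

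*Protocol article*

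**What the plan says.** All references are to the protocol article.

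- **Intercurrent events** defines the per-protocol set: "we will only include patients who completely adhered to the study protocol. This means that they are not allowed to skip study medication". On a skipped dose it continues: "If this happens, patients will be excluded from the secondary analysis". No threshold, time limit or exception is written.
- The same section says of the primary analysis: "Treatment discontinuation will be ignored in the primary analysis". On fatal events it says: "Death as an intercurrent event will be included as an outcome event in the analyses (both in ITT and PP"), provided the adjudication committee attributes the death to PE or bleeding. There is no matching sentence for non-fatal VTE or major bleeding.
- It also promises a report of non-adherence, "including details on the number of skipped dosages and the reasons for non-adherence".
- **DISTINCT-1 statistics** ranks the analyses: "A primary modified ITT analysis and a secondary PP analysis will be performed". DISTINCT-3 statistics uses the same ranking.
- **Study follow-up**, Table 1, marks "Treatment compliance (questionnaire") once, at 6 weeks.
- **Study interventions** sets the dosing periods. The DISTINCT-1 intervention is "administered until hospital discharge", with a single dose for same-day surgery; its control is 4 weeks. The DISTINCT-3 intervention runs to 6 weeks, twice daily from day 3; its control is 4 weeks.

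**The concern.** There are two separate problems.

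1. **Unequal selection by arm.** This follows from the text as it stands. A rule of no missed dose is far easier to meet over one or two in-hospital doses than over 4 weeks at home, and harder over 6 weeks than over 4. In DISTINCT-1 an almost unselected short arm would be compared with only the perfectly adherent controls. Randomisation no longer protects that comparison.

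2. **Possible selection by outcome.** This depends on how the rule is read. A patient whose study medication is stopped because of a non-fatal VTE or major bleed has not taken every allocated dose. Applied literally, the rule removes that patient and the event. More events fall within a longer dosing period, so the loss would again be unequal.

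In a non-inferiority trial the per-protocol result is the natural check that poor adherence has not hidden a difference. A set selected in these ways serves that purpose badly.

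**Working it through.** **Plan's own figures first.** DISTINCT-1, from Sample size: 0.75% in both arms, margin 1 percentage point, one-sided alpha 0.025, power 90%.

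n per arm = (1.960 + 1.282)² × 2 × 0.0075 × 0.9925 / 0.01² = 1564.3, rounded up to 1565. The total is 3130, as stated. With 10% dropout, 1565 / 0.90 = 1739 per arm, as stated.

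**Step 1: share excluded by the zero-miss rule.** The document gives no miss rate, so q = 0.5% and 1% per dose are assumptions, with misses independent. Share excluded = 1 − (1 − q)^d.

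Dose counts d:
- 2 for a short stay (the Introduction cites 1–2 days in fast-track studies);
- 28 or 56 for 4 weeks once or twice daily (the document leaves the agent to local protocol);
- about 80 for the DISTINCT-3 intervention (3 daily doses on days 0–2, assumed once daily, plus 39 days × 2 = 81).

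| Doses | q = 0.5% | q = 1% |
|---|---|---|
| 2 | 1% | 2% |
| 28 | 13% | 25% |
| 56 | 24% | 43% |
| 80 | 33% | 55% |

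Independence makes these high. If the miss rate varies between patients with mean 1% (beta distribution, shape 0.3, also an assumption), the shares for 28, 56 and 80 doses fall to 18%, 27% and 33%. The imbalance between short and long regimens remains.

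**Step 2: effect on DISTINCT-1 per-protocol power, before any bias.** Power = Φ(0.01 / √[0.0075 × 0.9925 × (1/n_control + 1/n_short)] − 1.960).

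- Losing 25% or 43% of controls from 1565 per arm: 0.85 or 0.79.
- The same losses from the 1739 enrolled: 0.89 or 0.83.

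The first pair spends the whole dropout allowance before adherence losses; the second spends none of it. The reduction from 0.90 is modest to moderate.

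**Step 3: the literal reading, with non-fatal events removed.** If a share f of an arm's events is dropped, the per-protocol risk is p(1 − f) / [p(1 − f) + 1 − p]. The document gives no event timing, so f is assumed. The starting case takes dosing days over 90: 2/90 = 2%, 28/90 = 31%, 42/90 = 47%.

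*DISTINCT-1, true risk 0.75% in both arms:*
- f = 31% control, 2% short: 0.52% versus 0.74%, a false difference of +0.22 points. The probability of showing non-inferiority is 0.79 instead of 0.90 at 1565 per arm.
- f = 80% control, 10% short: 0.15% versus 0.68%, +0.53 points, probability 0.55.

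*DISTINCT-3, planned 2.5% versus 1.25% for VTE and 0.5% versus 0.83% for major bleeding:*
- Control VTE: 0.025 × 0.69 / (0.025 × 0.69 + 0.975) = 1.74%.
- Intervention VTE: 0.0125 × 0.53 / (0.0125 × 0.53 + 0.9875) = 0.67%.
- The VTE risk ratio is 0.38 instead of 0.50.
- Major bleeding becomes 0.35% versus 0.44%, risk ratio 1.28 instead of 1.66.
- With no true VTE effect (2.5% in both arms), the risk ratio would be about 0.77.
- With f = 70% control and 80% intervention, the VTE ratio is 0.33 and the bleeding ratio 1.11.

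**The case against.** - **The text does not say that outcome-driven stops are excluded.** A reader might infer that the plan deletes every patient who stopped because of a VTE or bleed. Intercurrent events does not state this. Skipping a dose need not cover a stop made because of an endpoint, and keeping fatal events in the per-protocol analysis suggests that the authors do not want outcomes deleted. In DISTINCT-3, a patient whose step to apixaban is delayed for wound bleeding has followed Study interventions. This stands: problem 2 is conditional on a literal reading. Problem 1 is not.
- **A reader might infer that the rule could produce a false non-inferiority claim.** It would not do so for VTE. Removing more control events makes the short regimen look worse.
- **The analysis is secondary.** This stands. The modified ITT analysis ignores discontinuation and keeps these events, and no stated conclusion depends on the per-protocol result.
- **Reasons for non-adherence will be reported.** This would show how many exclusions followed an event, so it goes too far to say that a discordant result could not be interpreted. Reporting describes the exclusions but does not restore the comparison.
- **The SAP may settle it.** It could add the cut-off at the first event. A tolerance, however, would contradict the rule that the protocol article already states.

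**Conclusion.** The point holds as a fault in a secondary analysis set that should be fixed. It is not a flaw in the primary inference.

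- **Certain from the text:** no missed dose is tolerated, no cut-off at the first event is stated, and scheduled dosing differs greatly by arm. Unequal exclusion follows at any non-zero miss rate.
- **Dependent on assumptions:** the size of that exclusion. The percentages rest on assumed per-dose rates and independent misses, and are lower if misses cluster.
- **Dependent on a literal reading and on unknown event timing:** the loss of non-fatal events and the resulting bias. Its direction differs by trial: against the short regimen on VTE in DISTINCT-1, and towards the intervention on both VTE and major bleeding in DISTINCT-3. Only adjudicated fatal PE or bleeding is expressly protected.

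**What to change.** In the per-protocol definition under Intercurrent events:

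1. Judge adherence only up to the earliest of first adjudicated VTE, first adjudicated major bleed, death or end of scheduled dosing. State that a patient adherent until then stays in the set with the event.
2. Replace the ban on any skipped dose with a prespecified proportion of allocated doses, the same in both arms. The exact threshold is the sponsor's choice.
3. Keep the zero-missed-dose set as a sensitivity analysis only.

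The cost is a wording change and minor programming. The article reports recruitment under way, so the change can still be prespecified. The downside is a slightly less pure per-protocol set.

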### Analysis of primary endpoints

#### DISTINCT-1 statistics

A primary modified ITT analysis and a secondary PP analysis will be performed. The overall cumulative incidences of symptomatic VTE and major bleeding between the control and intervention groups will be compared, using a one-sided non-inferiority analysis for the absolute risk difference, with a significance level set as a one-sided p value of 0.025.

#### DISTINCT-2 statistics

Overall cumulative incidences for symptomatic VTE and major bleeding for the whole cohort will be estimated with a 95% CI.

#### DISTINCT-3 statistics

A primary modified ITT analysis and a secondary PP analysis will be performed. The overall cumulative incidences of symptomatic VTE and major bleeding between the control and the intervention groups will be compared, using a superiority analysis for the risk difference. The 95% CI for the absolute difference in event risks will be determined.

### Analysis of secondary endpoints

Risks of CRNMB, minor bleeding, PJI, myocardial infarction, ischaemic stroke and death will be estimated and compared between groups in a similar fashion. Functional and quality-of-life outcomes at 1 year postoperatively in patients who experienced symptomatic VTE, major bleeding or PJI and in controls will be compared between groups, across all groups.

We expect that the intervention will improve health outcomes at lower healthcare and societal costs. A cost-utility analysis will be performed using a Markov model to estimate the lifelong impact of VTE and bleeding events on discounted QALYs and societal costs. The intervention group will be compared with the control group according to ITT, separately for the DISTINCT-1 trial and the DISTINCT-3 trial.

The 3-month symptomatic VTE and bleeding rates (from the primary analysis) will be estimated from the trial. The impact per event on QALYs (ie, estimated using the EQ-5D), as well as on healthcare and productivity costs, will be estimated from the differences in patient-reported questionnaires preoperatively and after 14 days, 30 days, 90 days and 12 months. Medication and other healthcare will be valued using Dutch reference prices. QALYs and costs will be compared using net-benefit analysis, taking data and parameter uncertainty into account and with multiple imputation to account for missing data. Sensitivity and scenario analyses will include perspective (societal vs healthcare) and the valuation of productivity (friction costs vs human capital approach).^33^

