## Introduction

 Venous thromboembolism (VTE)^1^ primarily affects the deep veins of the leg (deep vein thrombosis (DVT)) and the pulmonary arteries (pulmonary embolism (PE)^2^). VTE is not only associated with considerable chronic morbidity leading to loss of quality of life but also with mortality. Patients undergoing elective total hip arthroplasty (THA) or total knee arthroplasty (TKA) have a high risk of postoperative VTE. Therefore, guidelines recommend prophylactic anticoagulant therapy after THA and TKA for all patients, although the type and length of treatment are under debate and differ between guidelines.^3^,^5^

Despite pharmacological thromboprophylaxis, 1.0%–1.5% of all patients still develop symptomatic VTE after THA/TKA.^6^ The main problem with the current ‘one-size-fits-all’ approach is that patients are considered to have an equal risk of thrombosis, while in reality, various individual and surgery-related factors influence VTE risk. For example, fast-track surgery protocols,^7^ which involve early mobilisation with subsequent reduction of hospital stay and opioid-sparing anaesthesia protocols, have greatly reduced VTE risk.^8^ Multiple studies have shown that in a large unselected population of patients undergoing THA/TKA, the incidence of VTE following fast-track surgery is <1.0% within 3 months, even when thromboprophylaxis was only administered during hospital admission (1–2 days).^8^,^11^ This implies that a large group of patients might currently be overtreated with thromboprophylactic therapy and are unnecessarily exposed to its burden and associated risk of bleeding. Major bleeding occurs in at least 0.5% of anticoagulated patients after THA/TKA, and minor bleeding, including clinically relevant non-major bleeding (CRNMB), occurs in about 6%.^12 13^ In addition to the general morbidity related to bleeding, a large surgery site-related haematoma increases the risk of an implant-associated infection and, therefore, the likelihood of revision surgery.^14^ Moreover, bleeding leads to prolonged wound drainage, which necessitates extended hospitalisation.^15^

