### Study objectives

The DISTINCT (inDividual, targeted thrombosIS prophylaxis versus the standard ‘one-size-fits-all’ approach in patients undergoing Total hIp or total kNee replaCemenT) trial aims to tailor thromboprophylaxis based on an individual’s estimated VTE risk. This VTE risk will be predicted by the recently developed and externally validated Thrombosis Risk Prediction following total hip and knee arthroplasty (TRiP(plasty)) score, specifically designed to predict an individual’s 90-day postoperative VTE risk after THA and TKA.^18^ We hypothesise that:

In patients with a low 90-day postoperative VTE risk (predicted risk <1.0%), thromboprophylaxis can be safely shortened to in-hospital duration only, without increasing the VTE risk, potentially reducing the incidence of CRNMB and minor bleeds.In patients with a high 90-day postoperative VTE risk (predicted risk >1.5%), high-dose thromboprophylaxis for 6 weeks is more effective in preventing symptomatic VTE compared with the standard prophylaxis. In addition, we expect that the benefits of this approach outweigh the potentially increased risk of bleeding.

Patients with an intermediate 90-day postoperative VTE risk (predicted risk ≥1.0% and ≤1.5%) receiving standard prophylaxis will be included to validate the predicted VTE risk. In addition, this group acts as a safety margin to ensure patient safety for the abovementioned interventions.

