#### Secondary outcomes

CRNMB: any non-major bleeding requiring medical intervention by a healthcare professional, and/or leading to hospitalisation or an increased level of care and/or prompting a face-to-face evaluation.Prosthetic joint infection (PJI), defined according to the European Bone and Joint Society, as described by McNally *et al.*^24^Myocardial infarction, ischaemic stroke and death.Patient-reported outcome measures (EQ-5D (EuroQol 5-Dimension Quality of Life Questionnaire), Oxford Hip Score,^25^ Oxford Knee Score,^26^ Visual Analogue Scale (VAS) pain).Impact of events on quality-adjusted life years (QALYs) and societal costs.

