### Sample size

#### Sample size calculation: DISTINCT-1 trial

By only including patients with a predicted VTE risk of <1.0%, a 3-month cumulative incidence of symptomatic VTE of 0.75% is expected in the control arm. This risk is based on the results from the development and validation studies of the TRiP(plasty) score.^18^ Multiple observational studies among patients in fast-track treatment protocols have shown that the risk of postoperative symptomatic VTE is ≤1% or even <0.5% with the use of in-hospital thromboprophylaxis only.^6 8 10 11^ Therefore, we expect no reduced or increased VTE risk when thromboprophylaxis is limited to in-hospital use only. Hence, the expected risk in the short-duration prophylaxis group is also 0.75%. The non-inferiority limit is set at 1%, which represents the minimal clinically important difference.^27^ Considering a one-sided alpha of 0.025 and a power of 90%, this leads to a necessary sample size of 3130 patients. To account for a maximum dropout rate of 10%, we aim to include 1739 patients in each group, totalling 3478 patients.

The incidence of (any) bleeding following THA/TKA has been reported to range from 0.5% to 3%. This variation is mainly caused by differences in bleeding definitions and the completeness and accuracy of patient follow-up.^12 13^ Hence, exact estimations of bleeding risks are difficult to obtain. Based on the available literature, we estimate that shortening the duration of thromboprophylaxis has no effect on major bleeding rates. The estimated relative reduced risk for minor bleeding+CRNMB is approximately 29%–50%.^10^,^1228 29^

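### The DISTINCT-1 comparison of minor bleeding rests largely on self-report by patients who know their allocation; the bleeding-benefit conclusion should rest on blindly adjudicated CRNMB

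*Protocol article*

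**What the plan says.** All references are to the Protocol article.

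- **Hypothesis.** Study objectives says of shortened prophylaxis in low-risk patients: "potentially reducing the incidence of CRNMB and minor bleeds". The DISTINCT-1 sample size section assumes that "shortening the duration of thromboprophylaxis has no effect on major bleeding rates" and adds: "The estimated relative reduced risk for minor bleeding+CRNMB is approximately 29%–50"%. It assumes the same VTE risk, 0.75%, in both arms.
- **Analysis.** The section on the analysis of secondary endpoints states: "Risks of CRNMB, minor bleeding, PJI, myocardial infarction, ischaemic stroke and death will be estimated and compared between groups in a similar fashion".
- **Outcome list.** Secondary outcomes lists CRNMB but not minor bleeding. CRNMB is any non-major bleed that needs medical intervention, leads to hospitalisation or more care, "and/or prompting a face-to-face evaluation".
- **Ascertainment.** Under Study follow-up, outcomes are assessed by questionnaire at 2 weeks, 6 weeks and 90 days. For a possible event, further data, "including imaging studies, consult letters, discharge letters and any other relevant information, are collected from the medical record of the participant".
- **Blinding.** Under Randomisation, blinding and treatment allocation, patients and treating physicians know the allocation and outcome assessors do not. Study design describes blinded outcome adjudication for the trial as a whole.

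**The concern.** CRNMB is defined so broadly that a face-to-face evaluation is enough. If minor bleeding is a separate category, it is what remains: bleeds handled without such contact. These will often have no imaging, consult letter or discharge letter for a blinded assessor to read. What is counted then depends mainly on what the patient chooses to report.

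The arms differ in a way that could affect reporting. After discharge, one arm takes an anticoagulant for the rest of the 4 weeks and the other takes none. Patients who know they are anticoagulated may be more alert to bruises or nosebleeds and more ready to report them. That would make short prophylaxis look better, which is the hypothesised direction. A blinded assessor can classify a reported event but cannot recover one that was never reported.

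At stake is the bleeding benefit claimed for DISTINCT-1. No change is expected in VTE or major bleeding, so among the trial's bleeding outcomes the expected gain lies in CRNMB and minor bleeding.

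**Working it through.** **1. The plan's own figure.** The DISTINCT-1 sample size reproduces. With 0.75% in both arms, a margin of 1%, one-sided alpha 0.025 and 90% power:

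n per arm = (1.960 + 1.282)² × 2 × 0.0075 × 0.9925 / 0.01² ≈ 1564.3, rounded up to 1565, so 3130 in total. Allowing for 10% dropout, 1565 / 0.9 = 1738.9, so 1739 per arm and 3478 in total. The 1565 evaluable patients per arm are used below.

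**2. Inputs for the illustration.**
- True rate of non-major bleeding: 6% in both arms. The Introduction says that "minor bleeding, including clinically relevant non-major bleeding (CRNMB), occurs in about 6"%, so this figure contains CRNMB.
- Alternative true rate: 3%. The sample size section says: "The incidence of (any) bleeding following THA/TKA has been reported to range from 0.5% to 3"%. The two statements do not agree, so both rates are shown.
- True treatment effect: none.
- Reporting: 90% in the 4-week arm; 80%, 70% or 60% in the short arm. The documents give no reporting rates. These are assumptions, and so is the direction.

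**3. Formula.** Reported rate = true rate × reporting probability. With reported rates a (4-week) and b (short), SE = √[a(1−a)/n + b(1−b)/n]. The chance of a significant result favouring short prophylaxis is Φ((a−b)/SE − 1.96). With equal reporting it is 2.5%.

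**4. Upper case: every non-major bleed is subject to the reporting difference.**

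| True rate | Short-arm reporting | Reported, 4-week v short | Apparent reduction | Chance of significance |
|---|---|---|---|---|
| 6% | 80% | 5.4% v 4.8% | 11% | 12% |
| 6% | 70% | 5.4% v 4.2% | 22% | 35% |
| 6% | 60% | 5.4% v 3.6% | 33% | 68% |
| 3% | 80% | 2.7% v 2.4% | 11% | 8% |
| 3% | 70% | 2.7% v 2.1% | 22% | 19% |
| 3% | 60% | 2.7% v 1.8% | 33% | 40% |

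For the third row, SE = √[(0.054 × 0.946 + 0.036 × 0.964)/1565] = 0.0074, and 0.018/0.0074 = 2.43, so Φ(0.47) = 68%.

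**5. Lower case: half of the 6% is CRNMB, reported at 90% in both arms.** The 50:50 split is an assumption. At 60% short-arm reporting of the minor bleeds:
- 4-week arm: 0.06 × 0.9 = 5.4%.
- Short arm: 0.03 × 0.9 + 0.03 × 0.6 = 4.5%.
- Apparent reduction: 0.9/5.4 = 17%.
- SE = 0.00775 and 0.009/0.00775 = 1.16, so Φ(−0.80) = 21%.

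Under the same split, minor bleeding analysed on its own is the last row of the table: 2.7% v 1.8%, a 33% apparent reduction with a 40% chance of significance.

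**6. Against the expected effect.** The pooled artefact reaches the expected 29%–50% range only in the upper case at 60% reporting (33%). At 17% it falls short of the range.

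**The case against.** The strongest points on the other side are these.

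- **No definition of minor bleeding is given.** A reader might infer that a minor bleed by definition leaves no record, or that blinded assessors cannot measure it. The article does not support either. The Introduction counts CRNMB within minor bleeding, a bleed noted on the ward or handled by telephone may be on record without meeting the CRNMB definition, and assessors could classify questionnaire answers blind. What stands is that records will usually be thin, and that blind classification does not correct differential reporting.
- **No pooled analysis is planned.** A reader might infer that minor bleeding and CRNMB will be tested together. The pooled term appears only in the sample size section, as an estimate from the literature; the analysis section names the two separately. This stands, and it limits the point to the hypothesis and the separate comparison.
- **The 33% and 68% figures apply the reporting difference to CRNMB as well.** This stands. They are an upper case. Bleeds before discharge, when both arms receive prophylaxis, would also dilute the difference.
- **CRNMB shares the weakness.** It is found through the same questionnaire and depends partly on care-seeking. This stands too, but a reported CRNMB can be verified from a record, which is usually not so for a minor bleed.
- **The stakes are limited.** The primary analyses are of VTE and major bleeding, the hypothesis is worded as a possibility, and the article also cites treatment burden and cost. A reader might infer that the case for shortening depends on minor bleeding; it does not.
- **A condensed article may leave definitions and adjudication detail to the full protocol.** True, so the missing definition is not the point. The point is that the article itself hypothesises a benefit on an outcome it does not list and compares it in the same way as the listed ones.

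**Conclusion.** The concern holds in a limited form. Minor bleeding is in the DISTINCT-1 benefit hypothesis and is compared between arms, yet it is absent from the outcome list and will rest largely on open-label self-report. A reporting difference plausibly favours short prophylaxis, and blinded assessment cannot correct it.

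Its size cannot be derived from the documents. Under assumed 90% v 60% reporting, a 6% true rate and 1565 per arm, the apparent reduction in all non-major bleeding lies between about 17% (21% chance of significance, if half are CRNMB reported equally) and 33% (68%, if all are affected). It is smaller with a milder reporting difference. These figures show what is possible and do not forecast bias. The primary VTE and major bleeding analyses are not touched by this point.

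**What to change.** - In Study objectives and Analysis of secondary endpoints, base the DISTINCT-1 bleeding-benefit conclusion on CRNMB, alone or with major bleeding, as confirmed from the medical record by the blinded assessors.
- In Secondary outcomes, list minor bleeding and label it as open-label patient-reported data.
- Report minor bleeding separately and descriptively, and do not pool it with CRNMB for any conclusion.

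**Cost.** Wording only, with no new data collection. Recruitment is under way, so the change should be fixed before any comparison by arm is seen. The bleeding-benefit comparison will have fewer events and less power. CRNMB still depends partly on questionnaire reporting and care-seeking, so the bias is reduced and not eliminated. This is an inexpensive improvement and does not repair a failure of the design.
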